## Abstract

**Background:**

The Eating Disorders Genetics Initiative 2 (EDGI2) is designed to explore the role of genes and environment in anorexia nervosa, bulimia nervosa, binge-eating disorder, and avoidant/restrictive food intake disorder (ARFID) with a focus on broad population representation and severe and/or longstanding illness.

**Methods:**

A total of 20,000 new participants (18,700 cases and 1,300 controls) will be ascertained from the United States (US), Mexico (MX), Australia (AU), Aotearoa New Zealand (NZ), Sweden (SE), and Denmark (DK). Comprehensive phenotyping and genotyping will be performed for participants in US, MX, AU, NZ, and SE using the EDGI2 questionnaire battery and participant saliva samples. In DK, case identification and genotyping will be through the National Patient Register and bloodspots archived near birth. Case–control and case-case genome-wide association studies will be conducted within EDGI2 and enhanced via meta-analysis with external data from the Eating Disorders Working Group of the Psychiatric Genomics Consortium (PGC-ED). Additional analyses will explore genetic correlations between eating disorders (EDs) and other psychiatric and metabolic traits, calculate polygenic risk scores (PRS), and leverage functional biology to evaluate clinical outcomes. Moreover, analyzing PRS for patient stratification and linking identified risk loci to clinically relevant phenotypes highlight the potential of EDGI2 for clinical translation.

**Discussion:**

EDGI2 is a global expansion of the EDGI study to increase sample size, increase participant representation across multiple ancestral background*s*, and to include ARFID. ED genetics research has historically lagged behind other psychiatric disorders, and EDGI2 is designed to rapidly advance the study of the genetics of the major EDs. Exploring EDs at both the diagnostic level and the symptom level will provide an unprecedented look at the genetic architecture underlying EDs.

**Trial registration:**

EDGI2 is a registered clinical trial: clinicaltrials.gov NCT06594913. https://clinicaltrials.gov/study/NCT06594913 (posted September 19, 2024).

## Background

We describe the *Eating Disorders Genetics Initiative 2* (*EDGI2*), a multi-national study designed to expand genomic discovery across four major eating disorders (EDs) (including AN [anorexia nervosa], BN [bulimia nervosa], BED [binge-eating disorder], and ARFID [avoidant/restrictive food intake disorder]). EDGI2 expands the work of EDGI [1] and the Eating Disorders Working Group of the Psychiatric Genomics Consortium (PGC-ED), and previous investigations including the Anorexia Nervosa Genetics Initiative (ANGI) [2] that identified eight significant loci associated with AN and intriguing genetic correlations (*r*_*g*_) with both psychiatric and metabolic/anthropometric traits, strongly suggesting that AN is a metabo-psychiatric disorder [3]. A genome-wide association study (GWAS) on binge-eating behavior suggested similar psychiatric genetic correlations as AN but divergent direction of metabolic/anthropometric genetic correlations [4]. EDGI2 expansion emphasizes recruitment of a broader range of people with EDs and a particular focus on people with longstanding and/or severe forms of the illnesses whose genomes may be enriched for causal variants.

## Methods

### Study aims

#### Aim 1: Extend EDGI core business by increasing sample size, populations, and ED phenotypes

We will ascertain, phenotype, and collect biosamples from ~ 20,000 people with AN, BN, BED, and/or ARFID (i.e., cases) and controls, increasing the total meta-analysis sample size to ~ 80,000 cases and ~ 730,000 controls. Collaboration with relevant groups will help attain the goal of enrolling 30% of cases from groups that have been less represented in previous ED research. EDGI2 also focuses on enrolling people with severe and/or longstanding AN, as their DNA may reflect higher genetic burden.

#### Aim 2: Apply statistical genetic analyses to better understand the heterogeneity and underlying biology of EDs

A multistage approach will implement a state-of-the-science pipeline for ED genomics. Primary analyses will include a GWAS of diagnoses, component behaviors, and dimensional traits, followed by case-case comparison, SNP-heritability (SNP-h^2^), genetic correlations (*r*_*g*_), polygenic risk scores (PRS), rare copy number variant (CNV) analyses, and bioinformatic integration for meaningful translation of GWAS results. Detailed phenotypes and PRS will be used for patient stratification, comparing standard diagnostic approaches with a novel, data-driven taxonomy of EDs. Finally, we will evaluate the hypothesis that AN is a "metabo-psychiatric disorder" by clarifying its relationship with metabolic and anthropometric traits through linkage disequilibrium score regression (LDSC), pathway-based PRS analysis (PRSet), phenome wide association study (PheWAS), Mendelian randomization (MR), and other emerging methods.

#### Aim 3: Evaluate genetic and environmental risk and resilience factors to inform risk prediction

Genetic or molecular groupings and patterns across cases and controls will be investigated through phenotypically characterizing individuals in the highest and lowest deciles of PRS based on clinical and phenotypic outcomes, and by genetically characterizing the top and bottom deciles of clinical severity across various PRS and PRS pathways. We will compare high-PRS cases with high-PRS controls to identify potentially protective environmental and genetic factors.

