##### Polygenic Risk Score

PRS aggregate risk alleles across the genome, weighted for effect size, to provide an estimate of an individual’s risk for a disorder or trait. We will compare two methods, the classical *P*-value thresholding method and SBayesRC [57], and implement appropriate cross-population approaches, for example PRS-CSx [58]. Exclusion criteria for *P*-value thresholding include uncommon SNPs (MAF < 0.01), low quality variants (imputation INFO score < 0.7), indels, strand ambiguous SNPs, and SNPs within the highly variable extended MHC region (chr6:25–34 Mb). As standard, SNPs will be LD pruned and clumped. *P*-value thresholds are predefined (0.001, 0.01, 0.05, 0.1, 0.5). We will use SBayesRC to calculate PRS while modeling LD.

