##### Rare CNV Analyses

To explore rare CNVs, we will use a clustering approach. CNVs will be called with validated complementary calling algorithms, iPattern [59], PennCNV [60], and QuantiSNP [61] in EnsembleCNV [62], which enables highly accurate CNV calling from SNP array data. Stringent QC include: exclusion of LogRDev Z > 2, BalleleDev Z > 2, or fragmented CNVs; samples with < 98% call rate, autosomal heterozygosity greater than five, unresolvable sex mismatch, unreliable calls (low-confidence score, < 10 probes, or only called by a single algorithm) will be excluded; and spurious calls will be filtered with QC CNV metrics, small CNVs, or CNVs where > 50% overlaps low confidence genomic regions, or hypervariable regions in white blood cells will also be excluded. Adjacent CNVs overlapping by > 75% will be annealed. Additional QC will be applied as necessary to DK bloodspots [63] and analysis may be limited to CNVs relevant to neuropsychiatric disorders (*N* = 53) [64–66]. Batch-wise Firth logistic regression (including covariates) will test CNV burden in cases and controls, followed by standardization of results with Stouffer’s signed Z-value meta-analysis. Rare CNV burden parameters include count, total and average length (kilobases [kb]), number of protein coding genes implicated, and total overlapped evolutionarily constrained bases [67]. Additionally, novel CNVs will be detected with breakpoint analyses via Firth’s logistic regression.

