### Risk prediction (Aim 3)

A key outstanding question in complex trait genetics is how individuals with high genetic risk remain resilient (i.e., disease-free), while others with low genetic risk may develop disease. Here, we will compare high ED-PRS cases to low ED-PRS cases, and high ED-PRS cases to high ED-PRS controls to characterize ED risk and protective factors and parse the ‘gene x environment’ relationship [9]. For case-case comparison, we will meta-analyze case samples from EDGI, EDGI2, UK Biobank, and other biobanks. Low PRS cases will be investigated for environmental contribution to disorder development in the absence of high genetic risk. We will perform PheWAS with the following comparisons: top decile vs. bottom decile cases, top decile vs. all other cases, and low decile vs. all other cases. As pathway risk aggregation can differ from genome wide PRS, we will also compare pathway-PRS in high and low PRS cases to identify pathways with notable contribution to genetic risk or resilience. Similarly, we will then compare high PRS cases to high PRS controls to identify potentially protective environmental and genetic factors against disorder development despite the presence of overall genetic risk.

Finally, we will repeat clustering analyses as described in *‘Patient Stratification (Aim 2b)’*, using PRS scores as clustering variables in place of phenotype clustering [103]. ED GWAS (ANGI, EDGI, EDGI2, and ARFID Genes and Environment [ARFID-GEN]) are combined for maximum sample size, and PRS will be calculated for ED behaviors, psychiatric co-morbidities, and metabolic traits for each sample. PRS curve is nonlinear (disproportionally greater in those with the greatest PRS burden [104–106]) and will thus be categorized into quartiles as ordinal variables, from which Gower distance matrices will be derived and used as input for clustering. Our primary analysis will be case-based clustering but will additionally expand to case–control and control-only clustering (controls: ≥ 30 years old, no lifetime ED symptoms) for a more robust investigation. Clusters will be compared for diagnostic and symptomatic prevalence, and we will repeat PheWAS as described for PRS decile comparisons above.

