## Discussion

Over the past decade, ED genetics has made significant strides. The 2019 Watson et al. GWAS [3] opened the door for deeper inquiries regarding how genes related to both metabolic and anthropometric factors can impact risk for AN, independent of genes influencing BMI, and beyond the impact of genes related to other psychiatric disorders. Since then, we have documented a high twin-based heritability for ARFID [114] and conducted two large genomic studies of ARFID [115, 116], currently queued for genotyping. Moreover, EDGI samples (N ~ 18,000) from the US, AU, NZ, and DK are all queued for genotyping, which also contributes large numbers of samples from individuals from varied ancestries, improving the representativeness of ED GWAS.

EDGI2 extends our work both globally and scientifically. By setting high but achievable recruitment goals across affected populations, we will ensure that ED genetics includes genotypes from many populations to ensure that our results maximize the applicability of findings across different populations and enhance the scope of research participation to improve scientific understanding for all populations. By focusing on severe and/or longstanding EDs, we will identify individuals whose genomes may be enriched for causal alleles, while working toward clinical prediction models that incorporate genetic data that may enhance our ability to identify individuals at risk for poor outcomes early and to inform more personalized intervention. We will convert knowledge of genetic and environmental risk factors for EDs into biologically and clinically relevant and actionable insights. EDGI2 will generate new knowledge and yield an action plan for translating findings into biologically informed prevention and treatment interventions.

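### Aim 3 treats cases with a low PRS as lacking high genetic risk, but comparisons made among cases alone cannot separate environment from genetic liability that the PRS does not capture

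*Protocol article*

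**What the plan says.** In the protocol article, the Aim 3 paragraph under Study aims plans "phenotypically characterizing individuals in the highest and lowest deciles of PRS based on clinical and phenotypic outcomes". It attaches no interpretation to the low decile.

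The interpretation comes in the section Risk prediction (Aim 3). The opening question contrasts people at high genetic risk who stay well with others: "while others with low genetic risk may develop disease". The section then states: "Low PRS cases will be investigated for environmental contribution to disorder development in the absence of high genetic risk". The PheWAS comparisons listed are "top decile vs. bottom decile cases, top decile vs. all other cases, and low decile vs. all other cases", all among cases. Pathway-PRS is also to be compared between high- and low-PRS cases. The section gives no caveat about genetic liability outside the PRS or about selection on case status.

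Other sections recognise genetic risk that the PRS does not hold:

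- Polygenic Risk Score: "PRS aggregate risk alleles across the genome, weighted for effect size, to provide an estimate". The thresholding version excludes "uncommon SNPs (MAF < 0.01), low quality variants (imputation INFO score < 0.7), indels, strand ambiguous SNPs", together with the extended MHC region.
- Rare CNV Analyses: "Batch-wise Firth logistic regression (including covariates) will test CNV burden in cases and controls". No comparison by PRS decile is described.
- Discussion: "we have documented a high twin-based heritability for ARFID", without a figure.

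**The concern.** The Risk prediction section equates a low PRS with low genetic risk and uses that as the ground for looking at environment. In an unselected population a low PRS would say little about the other causes. Among people who are all affected it says a great deal: whoever reached the threshold with little help from the PRS must have had more from elsewhere. That remainder includes rare variants, CNVs and common-variant effects the score misses, as well as environment.

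A factor that is more frequent in low-PRS cases may therefore mark uncaptured genetic load. At stake is what Aim 3, which is meant to inform risk prediction, can conclude about this group.

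**Working it through.** The article states no figure on this point, so there is none to reproduce. The check is a liability-threshold model solved by numerical integration.

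**Inputs, all assumed because the article gives none**
- Total heritability of liability, h²: 0.3, 0.5, 0.7. The article says only that it is high for ARFID.
- PRS R² on the liability scale: 0.02, 0.05, 0.10.
- Lifetime prevalence K: 1%, 3%, 4%. The SNP-Heritability section says a range will be modelled but names no values.

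**Model**
- L = P + G + E, with independent normal parts. P is the PRS part, variance R². G is genetic liability not captured by the PRS, variance h² − R². E is environment, variance 1 − h². Total variance is 1.
- A person is a case if L > t, where t = z(1 − K).
- For a case with PRS part p, let a = (t − p)/√(1 − R²). Then E[G + E] = √(1 − R²) · φ(a)/(1 − Φ(a)).
- That excess splits between G and E in the ratio (h² − R²) : (1 − h²). The genetic share is f = (h² − R²)/(1 − R²).

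**Central example: h² 0.5, R² 0.05, K 1%, deciles cut among cases**

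f = (0.5 − 0.05)/(1 − 0.05) = 0.474. The mean of G + E is 2.88 in bottom-decile cases and 2.19 in top-decile cases.

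| Mean, liability SD | Bottom decile | Top decile | Bottom − top |
|---|---|---|---|
| PRS part | −0.25 | +0.52 | −0.77 |
| Unmeasured genetic | +1.36 | +1.04 | +0.33 |
| Environment | +1.52 | +1.15 | +0.36 |

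(Differences are from unrounded values.)

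- Of the non-PRS excess of 0.69, the genetic part is 0.33, or 47%.
- Total genetic liability in bottom-decile cases is (−0.25 + 1.36)/√0.5 = 1.57 genetic SD above the population mean, about the 94th percentile. In top-decile cases it is 2.20 genetic SD.

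**Genetic share of the offset over the grid**

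The share f depends only on h² and R², not on prevalence or on how the deciles are cut:
- lowest: (0.3 − 0.10)/(1 − 0.10) = 0.20/0.90 = 22%;
- highest: (0.7 − 0.02)/(1 − 0.02) = 0.68/0.98 = 69%.

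**Other results over the grid, deciles cut among cases**
- Unmeasured genetic liability is higher in bottom- than in top-decile cases in every scenario, by 0.12 to 0.63 liability SD.
- Environmental liability is also higher in every scenario, by 0.13 to 0.74 liability SD.
- Total genetic liability of bottom-decile cases is 0.40 to 2.12 genetic SD above the population mean. It is lower than in top-decile cases in every scenario.

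With deciles cut in the population the directions are the same. The unmeasured genetic difference is then 0.12 to 0.67 liability SD, and total genetic liability of bottom-decile cases is 0.11 to 2.10 genetic SD above the mean.

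**The case against.** The strongest reply is that the design does what it should. Low-PRS cases do carry more environmental liability and less total genetic liability than high-PRS cases, so they are a sensible place to look for environmental factors, and PheWAS is exploratory association. The section also compares pathway-PRS between the groups, so it does not treat low-PRS cases as free of genetic contributors. All of this stands. It limits the point to the absolute wording and to what may be concluded. It does not remove it: pathway-PRS is still a PRS, and the CNV test is described for cases against controls only.

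Four stronger readings are tempting, and the documents do not support them:

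- *Aim 3 claims environmental causation.* The text says contribution, and says it will be investigated.
- *The faulty premise is in the Aim 3 summary under Study aims.* That paragraph only plans to characterise the deciles.
- *Genes and environment make up equal parts of the offset.* That holds only near h² 0.5, and the article gives no h².
- *Low-PRS cases have high total genetic liability.* At h² 0.3 and R² 0.10 it is only 0.11 to 0.69 genetic SD above the mean, depending on prevalence and on how deciles are cut. What is raised in every scenario is the unmeasured part.

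A condensed article may also leave secondary analyses to a fuller plan, so the lack of a CNV comparison by decile is not in itself an error. The stated premise is.

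**Conclusion.** The premise in Risk prediction (Aim 3) is wrong as stated: a low PRS in a case does not show that high genetic risk is absent. Bottom-decile cases have more unmeasured genetic liability than top-decile cases throughout the assumed grid, and it accounts for about 22–69% of the non-PRS offset. The contrast therefore cannot assign differences between PRS deciles to environment alone. It remains legitimate as exploration.

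The direction follows from conditioning on case status in an additive model with independent components and some heritability outside the PRS. The sizes rest on assumed h², R² and prevalence. Gene–environment correlation and interaction are not modelled. The correction is modest and cheap, but it changes what Aim 3 can claim, so it should be made.

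**What to change.** Change only the section Risk prediction (Aim 3).

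1. Replace the closing clause of the sentence on low-PRS cases with *with a low measured common-variant score*.
2. Add that differences between PRS deciles of cases may reflect uncaptured genetic liability and selection on case status as well as environment.
3. In the samples with CNV calls under Rare CNV Analyses, compare rare-CNV burden and neuropsychiatric-CNV carriage between bottom- and top-decile cases and between each of these deciles and the remaining cases. Show the environmental contrasts with and without adjustment for these, as a sensitivity analysis.

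The cost is a change of wording and reuse of CNV calls already planned for the EDGI2 samples. The claim becomes more modest. CNVs recover only part of the missing liability, so adjusting for them does not settle the question. The case-case comparison also pools UK Biobank and other biobanks, for which no CNV calls are described, so the sensitivity analysis may cover only part of the cases. Family history is not proposed as a comparator, because the article mentions first-degree relatives only as a control exclusion and does not show that this is collected in cases.

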#### Aim 4: Determine where in the body EDs “live.”

First, the "Gwas2cells" method will be used to identify brain cell types and anatomical regions implicated by genomic studies of EDs, and these findings will be contrasted with those for psychiatric disorders, neurological diseases, metabolic diseases, and brain-related traits. We will then identify gene-tissue associations across disease-relevant tissues and cell types, and leverage single-nucleus RNA sequencing (snRNA-seq) atlases to pinpoint brain cell types strongly implicated in the genomics of each ED and predict genetically regulated gene expression (GREx) in ED-relevant tissues and cells. Dynamic GREx will model gene expression in ED-relevant contexts, such as sex, body mass index (BMI),^1^ or stress, enabling precise and personalized modeling of gene expression changes under hypothetical scenarios like weight gain/loss, stressful life events, or depression.

#### Aim 5: Translational Summit

A Translational Summit in the final year will include leaders from genomics, neuroscience, interventional psychiatry, pharma, treatment, and community stakeholders. The summit will focus on strategies for optimizing and channeling the results of the study into a translational roadmap aimed at enhancing the prevention and treatment of EDs.

### Participants

EDGI2 will recruit 20,000 participants from the United States (US), Mexico (MX), Australia (AU), New Zealand (NZ), Sweden (SE), and Denmark (DK); within this recruitment target we will enroll ~ 3000 individuals with longstanding and/or severe AN. Effort will be made to enroll individuals who have been less frequently studied including those with varying body sizes and males. The minimum adult age for inclusion will vary by country: 16 in NZ and SE; 18 in US, AU, and MX; and 21 in Puerto Rico, with no upper age limit. Child case participants will be included for MX (15–17 years of age) and must have parent/guardian consent to participate. DK participants will all be born in DK between 1981 and 2008.

### Inclusion criteria

#### Case definitions

Participants from US, MX, AU, NZ, and SE will be selected based on self-reported lifetime Diagnostic and Statistical Manual of Mental Disorders-fifth edition (DSM- 5) criteria for AN, BN, BED, and/or ARFID via the ED100K.v4 ED online questionnaire, revised from the previous version (ED100K.v3) to include ARFID [2]. The ARFID portion contains items developed by the study team in addition to adapted, lifetime versions of the Nine Item ARFID Screen (NIAS) [5] and Pica, ARFID, and Rumination Disorder ARFID Questionnaire (PARDI-AR-Q) [6]. In MX, those recruited through the Comenzar de Nuevo clinic will be identified based on clinical diagnosis. In DK, cases of AN and BN will be identified using International Classification of Diseases – 10 th Revision (ICD-10) codes (F50.0, F50.1 for AN; F50.2, F50.3 for BN). DK will not include ARFID or BED as no ICD-10 codes exist for these disorders. SE will link participants to diagnostic records from the Swedish National Patient Register and Quality Register (Riksät) that have been validated through diagnostic interviews with acceptable reliability [7].

For US, MX, AU, NZ, and SE, longstanding and/or severe AN (restricting or binge/purge AN subtype) will be captured by the EDGI2 battery and include AN duration ≥ 5 years, lowest illness-related BMI ≤ 15, ≥ 3 treatment periods, and above age 20 at enrollment. Severe cases with rapid weight loss who attain very low body weights will also be included. DK will use the Anorexia Nervosa Register-based Severity Index (AN-RSI), which creates a systematic and weighted combination of age at onset, inpatient treatments, outpatient readmissions, treatment length, and illness duration [8]. Modifications to the AN-RSI definition may be made based on emerging research.

